#### Quality of life (QoL)

*Quality of life (QoL)* after SRT will be calculated from the corresponding questionnaires. According to the respective scoring manuals, subscale and total scores will be calculated. Descriptive statistics for these continuous variables will be presented as described above, and comparisons between treatment groups at specific timepoints will be made.

#### Safety, (serious) adverse effects, AED use, and tolerability of SRT

*Safety, (serious) adverse effects, AED use, and tolerability of SRT* are all categorical measures that are registered at predetermined timepoints and presented as proportions (i.e., prevalence of adverse effects) and 95% confidence intervals. Comparisons between both treatment groups will be done using chi-square tests and will be presented as effect size and 95% confidence interval.

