#### Epileptic seizure evaluation

Continuously, epilepsy diary information will be collected with the aid of a mobile phone application (Helpilepsy, Overijse, Belgium [23]). In addition, a nightly epilepsy seizure detection device (Nightwatch, Leiden, the Netherlands [24]) will be provided to the patients with the aim to detect eventual nocturnal seizures. The Nightwatch measurements are connected to the Helpilepsy application to provide the patient and the research team a total data capture of events. Patients are asked to annotate the type of experienced seizure. A monthly data extraction will be performed. In addition, on an annual basis, a follow-up consultation is scheduled with the trial assistant to evaluate the post-treatment severity of epilepsy and determine the RAEC.

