#### Imaging

In order to carefully determine the EZ and all possible (a)symptomatic side effects, magnetic resonance imaging (MRI) will be performed for all patients before and 2 years after inclusion. The patients in the waitlist-control arm which are treated with SRT will also receive a post-treatment MRI, 4 years after inclusion (= 2 years after SRT). The MRI protocol includes T1, T2, and susceptibility weighted imaging, fluid-attenuated inversion recovery (FLAIR), inversion recovery pulse sequence (cs IR), diffusion tensor imaging (DTI), and functional MR imaging.

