### Roles and responsibilities

Maastro is the study sponsor and principal investigator of this study. Maastro has a liability insurance which is in accordance with article 7 of the Dutch Medical research Involving Human Subjects Act (WMO). Maastro also has an insurance which is in accordance with the legal requirements in the Netherlands (Article 7 WMO). This insurance provides cover for damage to research subjects through injury or death caused by the study. The insurance applies to the damage that becomes apparent during the study or within 4 years after the end of the study.

Study administration, management, and monitoring will be performed by the trial coordinators and qualified monitors within the Clinical Trial Office (CTO) Maastro.

The Radiotherapy Epilepsy Expert group (REEG) is involved in the PRECISION trial, which consists of 4 neuro-radiation oncologists experts in state-of-the-art central nervous system radiotherapy including stereotactic radiotherapy. Preliminary results of the study will be shared with the REEG to share knowledge on treatment plans, indications, target volumes, and potential adverse effects and to consult (inter)national colleagues for advice. In addition, the authors consult international neurosurgeons which have extensive experience with SRT for epilepsy.

A data safety monitoring board (DSMB) is established to assure independent trial supervision and will monitor the recruitment, the reported adverse events, and the data quality at least every 6 months or after the SRT treatment of 10 patients.

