For the patients treated with SRT, the risks are based on the location of the EZ. Information is available from treatment of patients with epilepsy, brain metastases, or benign brain lesions. Treatment-related side effects in patients with epilepsy were described in the review of Eekers et al. [17]. The most common acute side effects of SRT are headache, nausea, and/or vomiting caused by reversible intracranial edema and can be treated with corticosteroids [22]. Long-term side effects include transient neurological deficits and exacerbation of seizures, magnetic resonance imaging (MRI) changes, expected and mostly asymptomatic superior quadrantanopia (for lesions treated in the temporal lobe), ischemic events, cognitive changes [38], and radiation necrosis rarely leading to symptomatic edema or cysts requiring surgical intervention [6, 17]. If the EZ is close to the pituitary, potential risks can be estimated from the literature of treatment of patients with a pituitary tumor. Cerebral infarction has been described as a long-term complication of stereotactic radiotherapy of benign skull base tumors, mainly pituitary tumors (SIR 1.48 – 4.2) [39–41]. For patients with a pituitary adenoma, it is known that hypopituitarism can occur after conventional and stereotactic radiotherapy in 50% of the patients, 10 years after treatment [42–44]. However, in patients with a non-functional pituitary adenoma, 37–85% of the patients has already hypopituitarism at the start of diagnosis [45–47]. Deficit of hormone production after conventional radiotherapy of the pituitary with 45 Gy is 45–100% for GH, 18–30% for LH/FSH, 15–22% for ACTH, and 25% for TSH [48, 49]. Location in the eloquent cortex is associated with neurological complications in patients with brain metastasis [50, 51]; therefore, when the location of the EZ is within the eloquent areas, we can limit the dose prescription to 18 Gy. The possible side effects of SRT will be registered carefully and will be weighed against the anticipated gain in quality of life.

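### Adverse effects are to be summarised as prevalence at set timepoints, which taken literally undercounts short-lived toxicity; the main summary should be patients with at least one event over a fixed window

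*Protocol article*

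**What the plan says.** The paragraph on safety, adverse effects, drug use and tolerability (Protocol article, Statistical analysis) groups these outcomes and says they "are all categorical measures that are registered at predetermined timepoints and presented as proportions (i.e., prevalence of adverse effects"), with 95% confidence intervals. It continues: "Comparisons between both treatment groups will be done using chi-square tests and will be presented as effect size and 95% confidence interval".

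The Discussion (Known and potential risks and benefits) describes the toxicity expected: "The most common acute side effects of SRT are headache, nausea, and/or vomiting caused by reversible intracranial edema". Its list of long-term effects includes transient neurological deficits and seizure exacerbation.

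The article does not say which timepoints the safety paragraph means. The only schedule shown, Table 1, has columns for pre-SRT and for years 1 to 5, and no adverse-event row. Under Epileptic seizure evaluation, "on an annual basis, a follow-up consultation is scheduled with the trial assistant to evaluate the post-treatment severity of epilepsy and determine the RAEC". Under Imaging, "magnetic resonance imaging (MRI) will be performed for all patients before and 2 years after inclusion".

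Other passages bear on how events are captured:
- The abstract names Common Toxicity Criteria.
- Seizures are recorded continuously, and "A monthly data extraction will be performed".
- Use of co-intervention covers patients who have symptoms around SRT.
- The DSMB monitors reported adverse events.

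**The concern.** Prevalence at a timepoint counts patients who have the condition at that moment. For a lasting effect, such as a visual field defect, that is a sensible measure. For an effect that comes and goes between timepoints it is not, because a resolved event adds nothing to the proportion. The article expects both kinds, yet its stated summary serves only the first.

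The undercount is unlikely to be equal in the two arms. The waitlist group is offered SRT only after 2 years, so acute radiation effects before then arise only in the SRT arm. Losing them makes SRT look better tolerated than it is, in a trial meant to inform clinical practice and reimbursement and to weigh side effects against gains in quality of life.

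A smaller issue is the test. Chi-square is fixed for all these comparisons, although some of the events listed, such as symptomatic radiation necrosis, are described as rare. With 47 patients per arm the approximation is then poor.

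**Working it through.** **Denominator.** The sample size section gives 84 patients for analysis and 10% dropout: 84 / (1 − 0.10) = 93.3, rounded up to 94, or 47 per arm. This agrees with the article. The plan gives no expected adverse-event rate, so there is no safety figure to reproduce.

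**How much point prevalence counts (illustration).** Assumptions: one event per patient, onset uniform over 24 months, duration D months, counted only if ongoing at one of k equally spaced timepoints, the last at month 24. The share counted is k × D / 24, capped at 1.

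| Duration D | k = 2 (months 12 and 24) | k = 8 (every 3 months) |
|---|---|---|
| 1 week (0.25) | 2 × 0.25 / 24 = 2% | 8 × 0.25 / 24 = 8% |
| 1 month | 2 × 1 / 24 = 8% | 8 × 1 / 24 = 33% |
| 3 months | 2 × 3 / 24 = 25% | 8 × 3 / 24 = 100% |

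The k = 2 column uses Table 1's yearly visits. The k = 8 column is an assumed denser schedule, because the article does not tie the safety timepoints to Table 1. With k = 2, acute events that follow SRT directly and resolve within the year are not counted at all. Even quarterly timepoints lose most events of a month or less.

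**The test in sparse tables.** The counts below are illustrative. For a patients with an event in one arm, none in the other and 47 per arm:
- Smallest expected count = a / 2.
- Uncorrected chi-square = 94 × (47a)² / (47 × 47 × a × (94 − a)) = 94a / (94 − a).
- Two-sided Fisher p = 2 × C(47, a) / C(94, a).

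| Events | Smallest expected count | Uncorrected chi-square | p, uncorrected | p, continuity-corrected | p, Fisher |
|---|---|---|---|---|---|
| 3 v 0 | 1.5 | 282 / 91 = 3.10 | 0.078 | 0.241 | 0.242 |
| 4 v 0 | 2.0 | 376 / 90 = 4.18 | 0.041 | 0.125 | 0.117 |

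As a check for 4 v 0: 2 × (47 × 46 × 45 × 44) / (94 × 93 × 92 × 91) = 0.117.

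The uncorrected test crosses 0.05 at 4 v 0 and Fisher's test does not. The continuity-corrected chi-square almost agrees with Fisher's. The article does not say which form of chi-square it would use for safety.

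**The case against.** The strongest reply is that the wording is loose and the data are there. Prevalence appears only inside a parenthesis and may mean period prevalence, that is, patients affected at any time. Visits may ask about events since the last contact. The article names a toxicity scale, promises careful registration of side effects, records seizures continuously (which would show seizure exacerbation), provides for symptomatic patients around SRT, and refers to reported adverse events. Reporting procedures are normally left to the full protocol, which exists and is not shown.

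Much of this stands, and it rules out several stronger readings that a reader might infer.
- **That transient toxicity will be missed.** Nothing says that events between visits go unrecorded, and Table 1 is not presented as the adverse-event schedule. The lack of an adverse-event row is no finding in an article.
- **That the DSMB will review without data.** Its reviews take place "at least every 6 months or after the SRT treatment of 10 patients". At 2 to 3 patients per month and 1:1 allocation, the tenth SRT patient is expected at month 20/2 = 10.0 to 20/3 = 6.7, before any 1-year visit. But the board sees reported events, which need no 1-year visit, and an early review is a safeguard.
- **That imaging comes too late.** The trial MRI is meant "In order to carefully determine the EZ and all possible (a)symptomatic side effects" and follows at 2 years, but the article does not exclude clinically indicated imaging in between.
- **That the chi-square test itself favours SRT.** A p-value that is too small for excess events in the SRT arm works against SRT. The gap also nearly vanishes with a continuity correction.

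The direction of the undercount also needs a qualification. Controls who receive VNS or DBS can have short-lived effects of implantation, and these would be undercounted too.

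What the reply does not remove is the stated rule. If events are collected continuously, summarising them as prevalence at timepoints discards that information. If prevalence was meant as patients ever affected, the sentence should say so and name the window.

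**Conclusion.** The point holds as a matter of analysis choice. The safety paragraph fixes a summary that, read as written, undercounts short-lived SRT toxicity and would tend to favour SRT in the benefit-risk comparison. The size cannot be derived from the article, which gives no toxicity rates, durations or adverse-event timepoints. Under the stated assumptions, the share of events lasting a month or less that is counted runs from 2% to 8% with yearly timepoints and from 8% to 33% with quarterly ones. The direction assumes that acute effects of SRT are more frequent than short-lived effects of neuromodulation among controls.

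The choice of test is secondary. It matters only where expected counts are below 5 and the uncorrected chi-square is used. The documents do not support a conclusion that toxicity goes unrecorded, or that DSMB review or imaging is deficient.

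**What to change.** In the safety paragraph of the statistical section:
1. Make the main summary the proportion of patients per arm with at least one adverse event, shown separately for any grade, grade 3 or higher, and serious, from randomisation to 2 years. Use all reported events, with onset date and grade. The window is the same in both arms and ends before the waitlist group is offered SRT.
2. Keep point prevalence at visits as a supplement. It remains informative for lasting effects, and it is a natural summary for drug use.
3. Where any expected cell count is below 5, use Fisher's exact test, with a score-type 95% confidence interval for the difference in proportions.

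The cost is the wording of one paragraph and slightly more data entry if onset date and grade are not already collected. P-values for rare events become somewhat more conservative. The analysis change itself needs no extra visit or procedure.

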#### Cost-effectiveness

Decision analytical modeling will be used to estimate the cost-effectiveness of SRT compared to standard of care for adult patients with drug-resistant localized epilepsy not eligible for surgery. A state-transition model will be developed, to estimate and compare costs and (quality adjusted) life years for both treatment options. This decision analytic model will be developed in accordance with (inter)nationally recognized good practices [37], relevant technical support documents of the National Institute for Health and Care Excellence, and the Dutch Pharmaco-economic guideline (e.g., lifetime time horizon). To inform the model, utility (EQ-5D instrument) and resource use will be measured during study follow-up, while unit costs will be based on the Dutch cost guideline, and unrelated medical costs will be incorporated using the PAID tool. If required, published literature, clinical guidelines, hospital financial administration, and/or expert opinion will be used to inform input parameters. The structure and parameter estimates will be validated using expert consultation and uncertainty will be estimated using deterministic and probabilistic sensitivity analyses.

#### Neurocognition

For neuro-cognitive test variables, the Reliable Change Index (RCI) will be calculated by dividing the difference between pre-treatment (baseline) and posttreatment (2 year) scores by the standard error of the difference. The standard error of the difference will be defined based on the reference data from literature for each test. A RCI > 1.5 will be used to quantify as significant change. Differences in RCI between treatment and waitlist-control group will be compared and presented as effect size and 95% confidence interval.

A loss of follow-up is taken into account for 5 patients in each treatment arm. If patients withdraw from the study, patients will be referred back to the treating physician. Data collected until the time of withdrawal will be used for analysis, unless the patient decided his data must be destroyed.

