#### Cognitive evaluation

In order to determine possible side effects on cognitive functioning, an evaluation will be performed for all patients before and 2 years after inclusion. The patients in the waitlist-control arm which are treated with SRT will be planned for an evaluation 4 years after inclusion (= 2 years after SRT). Cognitive evaluation includes the Rey Auditory Verbal Learning Test (RAVLT [25]), Trail Making Test A and B (TMT-A; TMT-B [26]), Stroop test [27], Digit Span WAIS-IV [28], Dutch Reading Test for Adults (NLV, [29]), Fluency test (GIT [30]), and Letter Digit Substitution Test (LDST [31].

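### The one-signed cognitive rule RCI > 1.5 does not tell decline from improvement across the battery, its chance rate is unstated, and the between-arm comparison of RCI ignores the precision available from the baseline score

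*Protocol article*

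**What the plan says.** The Cognitive evaluation section gives the purpose: "In order to determine possible side effects on cognitive functioning, an evaluation will be performed for all patients", before and 2 years after inclusion. It lists eight measures: RAVLT, TMT-A, TMT-B, Stroop, Digit Span, NLV, a fluency test and LDST. It does not say how any of them is scored.

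The Neurocognition section obtains the RCI by "dividing the difference between pre-treatment (baseline) and posttreatment (2 year) scores by the standard error of the difference". On the denominator it says: "The standard error of the difference will be defined based on the reference data from literature for each test". The classification rule is that RCI > 1.5 "will be used to quantify as significant change". The group analysis is: "Differences in RCI between treatment and waitlist-control group will be compared and presented as effect size and 95% confidence interval".

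The section gives no absolute value or ± sign, no explicit order of subtraction, no alignment of direction between tests, no error rate for the rule and no reason for 1.5. A significance level of 0.05 appears only in the Sample size calculation and for the primary endpoint in Statistical analysis.

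**The concern.** The cognitive battery is there to find side effects of irradiating brain tissue, so the classification must identify decline. A single positive cut-off does this only if a positive RCI means decline on every test. A battery that mixes timed tests with tests where a higher score is better will not meet that condition unless the scores are re-oriented first. Real harm on some tests could then show up as fewer flagged patients, not more.

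Two further matters follow from the same paragraph. The word significant is attached to a cut-off whose chance rate is not given, so a reader cannot tell how many flagged patients to expect when nothing has changed. And the between-arm comparison uses the RCI itself, which is a change score divided by a constant for each test, although the baseline score is available as a covariate.

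**Working it through.** **Inputs.** From the article: cut-off 1.5; standard error taken from reference data for each test; 84 evaluable patients, so 42 per arm. Assumptions: with no true change the RCI is approximately N(0,1), meaning that the reference standard error fits and there is no practice effect; TMT-A, TMT-B and Stroop are scored as time (higher is worse); the other tests are scored so that higher is better.

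**The article's own figure.** It gives no error rate for the RCI rule, so there is none to reproduce. The patient number used below does reproduce: 50% against 15%, two-sided 0.05, power 0.90, pooled variance and continuity correction give 42 per arm, or 84. Dividing by 0.90 gives 93.3, which becomes 94, or 47 per arm.

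**Step 1: direction.** What a positive RCI means:

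| Order of subtraction | Higher-is-better tests | Timed tests |
|---|---|---|
| Baseline minus 2-year | decline | improvement |
| 2-year minus baseline | improvement | decline |

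In either row the literal rule flags decline on one group only and can never flag it on the other.

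**Step 2: what this does to a real decline.** Suppose every treated patient declines by 1 standard error of the difference on every test (illustrative).
- Tests where positive means decline: P(Z > 1.5 − 1) = P(Z > 0.5) = 0.309, so 42 × 0.309 ≈ 13 flags.
- Tests where positive means improvement: P(Z > 1.5 + 1) = P(Z > 2.5) = 0.006, so 42 × 0.006 ≈ 0.3 flags.
- No change: P(Z > 1.5) = 0.067, so 42 × 0.067 ≈ 2.8 flags.

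The same harm raises the count from 2.8 to 13 on one group of tests and lowers it from 2.8 to 0.3 on the other.

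**Step 3: chance rates by cut-off**, per test, no true change:

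| Cut-off | One-sided | Two-sided | Flags per 42, one- / two-sided |
|---|---|---|---|
| 1.5 | 6.7% | 13.4% | 2.8 / 5.6 |
| 1.645 | 5.0% | 10.0% | 2.1 / 4.2 |
| 1.96 | 2.5% | 5.0% | 1.05 / 2.1 |

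The literal rule belongs in the one-sided column. The 13.4% applies only to |RCI| > 1.5, and on that reading the direction fault of Step 1 is replaced by a count that mixes decline with improvement.

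**Step 4: price of a stricter cut-off.** Under the decline in Step 2, with direction aligned, detection is P(Z > 0.5) = 30.9% at 1.5, P(Z > 0.645) = 25.9% at 1.645 and P(Z > 0.96) = 16.9% at 1.96.

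**Step 5: between-arm precision.** With one standard error per test, the difference in mean RCI is the difference in mean change divided by a constant. With variance σ² at both visits and baseline/2-year correlation r, the change score has variance 2σ²(1 − r). The 2-year score adjusted for baseline has residual variance σ²(1 − r²). The ratio is (1 − r²) / [2(1 − r)] = (1 + r)/2. For r = 0.5 this is 0.75; for r = 0.8 it is 0.90. The article gives no r, so this range is an assumption.

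**The case against.** A critic can fairly say several things.

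- **Direction-neutral wording.** Difference and change are neutral terms, so |RCI| > 1.5 may be what is meant, and deterioration on timed tests would then be flagged. That is possible, but the printed rule carries one sign, and the two-sided reading still does not separate side effects from gains.
- **Detail left to the full protocol.** Score orientation might be set out there. This carries some weight. However, the article itself publishes the cut-off with its sign, so the stated rule is open to comment.
- **Unstated scoring.** The direction fault does rest on an assumption about how the tests are scored. This stands.
- **Sensitivity.** A looser cut-off is defensible for a harm measure. This also stands: in Step 4, moving to 1.96 cuts detection from 31% to 17% of patients.

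Stronger readings are tempting and are not supported. A reader might infer that the rule has a 13% error rate where 5% was promised. The article promises no rate for this rule, and 13.4% cannot be combined with the one-sided sign fault. A reader might infer that false flags bias or inflate the between-arm result. The chance rate is the same in both arms, and the stated comparison is of RCI, not of flags. Whether 1.5 dilutes a real difference in flag rates depends on the pattern of harm. With a uniform decline of 1 standard error, the looser one-sided cut-off separates the arms better (31% against 7%, compared with 17% against 2.5% at 1.96). If a few patients decline a lot, the stricter one can do better. Finally, the article describes no composite or any-test rule, so a per-patient false-flag rate across the whole battery is not a property of this plan.

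**Conclusion.** The point holds in limited form. As printed, the rule does not identify cognitive decline consistently: under the time-scoring assumption the literal version is blind to decline on one group of tests, and the two-sided version merges decline with improvement. The chance rate is 6.7% or 13.4% per test depending on the reading, about 2.8 or 5.6 patients per arm of 42, if the reference standard errors fit and there is no practice effect. The value 1.5 is not wrong in itself; it trades specificity for sensitivity and needs its rate stated. The between-arm comparison of RCI is valid, but gives up some 10% to 25% of variance for r between 0.8 and 0.5, with equal variances at both visits. The primary endpoint is untouched. Severity is minor to moderate, on a secondary safety endpoint.

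**What to change.** 1. State the order of subtraction and orient every test, reversing those where a higher score is worse, so that a negative RCI means decline throughout.
2. Report decline and improvement as separate counts by arm, for each test.
3. Say whether the cut-off is one- or two-sided. Either keep 1.5 and state its chance rate (6.7% per direction, 13.4% for both together), or, if 5% is intended, use 1.645 one-sided or 1.96 two-sided.
4. Make the between-arm comparison the 2-year score adjusted for its baseline value, with effect size and 95% confidence interval, and keep the RCI counts as descriptive support.

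Items 1, 2 and 4 change analysis wording only and need no new data, since both scores are already collected. A stricter cut-off under item 3 has a real cost: fewer patients with true decline would be flagged. All of this should be settled before the 2-year cognitive data are analysed.
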